**4.3 Subject information and informed consent**

The subjects should be provided with the main information of the study and informed consent. Prior to the start of the study, the investigators must provide the subjects with the written approval of the ethics committee/institutional review committee/approval of the informed consent and all other written information. The ethics committee/institutional review committee approval and the approved subject instructions/informed consent must be filed in the study document together.

Informed consent must be obtained before implementing any specific study steps. The date when the subjects participated in the study and signed the informed consent form should be recorded in the corresponding documents of the subjects.

**4.4 Secrecy**

All records of the patient's identity are kept confidential and will not be made public to the extent permitted by relevant laws and/or regulations.

The name of the subject will not be provided. Only subject number and abbreviation were recorded in case report form. If the subject's name appears in any other document (e.g. pathology report), the copy of the document must be erased. Research reports stored in computers must comply with local data protection laws. When the results of the study are published, the identity of the subjects will also be kept confidential.

The investigator will keep a list to identify the subjects' records.

1. **Statistical methods**

**5.1 Statistics analysis plan**

**5.1.1 The population for analysis**

Efficacy analysis will be conducted in the intention to treat population (ITT) and efficacy-evaluable population. The patients who did not have at least one post-baseline efficacy assessment were defined as not assessable for efficacy and were ruled out from the efficacy-evaluable population. The safety analysis included all patients in ITT population who had received at least one study medication. The analysis population of ORR refers to all patients with partial remission or complete remission determined by RECIST 1.1 in ITT population and efficacy-evaluable population.

**5.1.2 Baseline and demographic characteristics**

The baseline, demographic characteristics, baseline tumor characteristics, medical history, previous anticancer treatment, combination therapy, vital signs and termination of the trial were summarized. For continuity assessment, the mean, standard deviation, distribution range and median will be calculated. Absolute value, frequency and percentage will also be calculated.

**5.1.3 Efficacy analysis**

Efficacy analysis will be conducted in the intention to treat population (ITT) and efficacy-evaluable population.

**5.1.3.1 Primary Study Endpoint**

Primary endpoint：Objective Response Rate (ORR, complete or partial response according to RECIST version 1.1).

**5.1.3.2** **Secondary study endpoints**

Secondary study endpoints included disease control rate (DCR, the proportion of patients who achieved a complete response, a partial response, or stable disease), progression-free survival (PFS), overall survival (OS) as well as safety.

PFS was defined as the time from therapy initiation to progression according to RECIST.

OS is defined as the time from therapy initiation to death from any cause.

Depth of response (DPR) was defined the percentage of maximum tumor reduction achieved in treatment compared with baseline. In case of CR, DPR is 100%.

Remission maintenance time was calculated in all PR or CR patients who were confirmed to meet RECIST 1.1 criteria. The duration of remission is the time from the first record to PR or Cr until death or disease progression (based on the first occurrence). As of the date of analysis, the deadline was the date of their last imaging evaluation.。

Kaplan Meier method was used to get the expected survival curve of the patients including PFS and OS.

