| Statistical matters | Primary endpoint (In the intention-to-treat population and in the efficacy-evaluable):  The statistical criteria for main analysis will be based on the number of patients with the best overall response of Complete Response (CR) or Partial Response (PR) according to RECIST guideline version 1.1. An accurate confidence interval based on a binomial distribution is used for calculating the proportion of confidence intervals. ORR by RECIST 1.1  Secondary endpoint  The following analyses will be performed for ITT (Intention to Treat: ITT) and efficacy-evaluable population, SP (Safety Population).   1. DCR by RECIST 1.1(In the intention-to-treat population and in the efficacy-evaluable population): Confidence intervals for DCR will be created using the exact test according to a binomial distribution. 2. PFS, OS: A survival function will be estimated using the Kaplan-Meier method. The median with the 95% CI will be estimated. 3. Incidence of adverse events: As incidence of adverse events, in addition to tabulation of the frequency of adverse events, the incidence of Grade 3 or higher adverse events will be calculated. |
| Primary investigator | [name] |
| Planned study sites | Shanghai Changzheng Hospital |

Contents

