Secondary study endpoints: Disease Control Rate (DCR, the proportion of patients who achieved a complete response, a partial response, or stable disease), Progression-Free survival (PFS), overall survival (OS) as well as safety. PFS was defined as the time from therapy initiation to progression according to RECIST. OS is defined as the time from therapy initiation to death from any cause.

Exploration study endpoints: biomarker analysis including PD-L1 expression, TMB, molecular alteration profile, tumor immune-microenvironment, plasma exosome miRNA.

1. **Method**
   1. **Study design**

APICAL-CRC trial was an investigator-initiated, open-label, non-randomized, single-arm, phase II clinical trial using Simon’s minimax two-stage design. The combination of anlotinib plus sintilimab is expected to result in an improved ORR of 35%. The null hypothesis, which stated that the true ORR was 15%, would be tested against a one-sided alternative of 35%, with 80% power and a type I error rate of 5%. In the first stage, the study accrued 15 patients. If less than two response or no response was observed, the study was terminated and deemed negative. Otherwise, an additional 13 patients would be accrued for the second stage. The study was considered positive if there were more than 9 responders among the 28 patients.

- 1. **Single-arm**

This trial design is a single-arm study without control group.

- 1. **Participants**

According to the inclusion criteria, all patients required to be treatment-naïve advanced CRCs

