**3.7.1 Efficacy Evaluation**

The antitumor effect will be evaluated in accordance with RECIST version 1.1 every 6 weeks.

The primary study endpoints for the study were objective response rate (ORR, complete or partial response according to RECIST version 1.1).

Secondary study endpoints included disease control rate (DCR, the proportion of patients who achieved a complete response, a partial response, or stable disease), progression-free survival (PFS), overall survival (OS) as well as safety.

PFS was defined as the time from therapy initiation to progression according to RECIST.

OS is defined as the time from therapy initiation to death from any cause.

Depth of response (DPR) was defined the percentage of maximum tumor reduction achieved in treatment compared with baseline. In case of CR, DPR is 100%.

Remission maintenance time was calculated in all PR or CR patients who were confirmed to meet RECIST 1.1 criteria. The duration of remission is the time from the first record to PR or Cr until death or disease progression (based on the first occurrence). As of the date of analysis, the deadline was the date of their last imaging evaluation.

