**3.7.4.1 Treatment period**

- The screening phase should be conducted within 28 days before the start of study drug treatment.
- Treatment period refers to the interval from the use of the first drug treatment to the withdrawal of the patient from the study drug treatment.
- Patients will enter the post-treatment follow-up period after discontinuing the study drug treatment. This period should include contacting the patient every 3 months until 1 year after progression or recording the patient's death to collect the data of overall survival.

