**Remission time**

The remission time should be calculated from the time when CR or PR (no matter who was recorded first) was first met, until the date of recurrence or progression of the disease was first recorded.。

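### PFS is defined to end only at RECIST progression; with death left out, the Kaplan-Meier curve is time to progression and can only equal or overstate PFS

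*Protocol*

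**What the plan says.** Section 5.1.3.2 of the protocol reads: "PFS was defined as the time from therapy initiation to progression according to RECIST". Sections 2 and 3.7.1 repeat the sentence. The synopsis lists PFS as a secondary endpoint and gives its summary ("The median with the 95% CI will be estimated") but no event definition. Section 5.1.3.2 names the estimator: "Kaplan Meier method was used to get the expected survival curve of the patients including PFS and OS".

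Sections 3.7.1 and 5.1.3.2 do name death for two other endpoints. For OS: "OS is defined as the time from therapy initiation to death from any cause". For duration of remission, the period runs "until death or disease progression (based on the first occurrence". The RECIST appendix (Section 7.3, Remission time) then gives a second version of that period, which runs "until the date of recurrence or progression of the disease was first recorded" and does not mention death.

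Section 3.7.4.1 provides for survival follow-up after study drug is stopped, by "contacting the patient every 3 months until 1 year after progression or recording the patient's death".

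**The concern.** PFS is understood as time to progression or death, whichever comes first. The protocol's definition stops at progression. A patient who dies without documented progression then has no PFS event, and the natural handling in a Kaplan-Meier analysis is censoring. Censoring treats that patient as still able to progress later, at the same rate as those who remain under observation. The deaths concerned, from toxicity or from rapid decline before the first scan at about week 6, are among the worst outcomes in the trial.

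Two features of this protocol sharpen the problem. First, Section 5.1.1 removes patients without a post-baseline assessment from the efficacy-evaluable population. A death before the first scan is therefore excluded there and censored in the ITT population, so it counts as a PFS failure in neither. Second, the trial has a single arm. Its PFS can be read only against figures from elsewhere, and there is no control arm to carry the same bias. The introduction shows how such medians are used: it sets 6.3 months in one published study against 1.9 and 3.2 months in two others.

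**Working it through.** **1. The definitions side by side**

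| Endpoint | Where | Progression ends it? | Death ends it? |
|---|---|---|---|
| PFS | Sections 2, 3.7.1, 5.1.3.2 | Yes | Not named |
| OS | Sections 2, 3.7.1, 5.1.3.2 | No | Yes, any cause |
| Duration of remission | Sections 3.7.1, 5.1.3.2 | Yes | Yes, whichever is first |
| Remission time | Section 7.3 | Yes (or recurrence) | Not named |

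Take a responder who dies without progression. Under Section 3.7.1 the remission ends at death, but PFS as defined there does not. Under Section 7.3 the remission does not end either.

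**2. Direction of the error**

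Compare two Kaplan-Meier curves on the same patients, one counting a death without progression as an event and one censoring it at the date of death. The patient leaves the risk set on the same day in both, so the risk sets are identical. At that death the first curve is multiplied by (1 - 1/number at risk) and the second is left unchanged. The progression-only curve therefore lies on or above the PFS curve throughout.

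**3. Size**

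The protocol gives no assumed PFS, event count or power for PFS, so there is no figure of its own to reproduce. The inputs are:

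- s, the share of first events that are deaths without documented progression: an assumption, 0 to 30%.
- Constant hazards: an assumption.
- The true median m: 8 months as an assumed illustration, and 6.3 months, the median the introduction reports for an earlier kinase inhibitor plus anti-PD-1 study. Neither is a forecast for this trial.

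Let the total hazard be h = ln 2 / m. Censoring the deaths leaves the progression hazard (1 - s)h. The apparent median is ln 2 / [(1 - s)h] = m/(1 - s), and the apparent 12-month rate is exp[-12(1 - s)h].

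| s | Factor 1/(1-s) | Median if true value is 8 | Median if true value is 6.3 | 12-month rate if true median is 6.3 |
|---|---|---|---|---|
| 0 | 1.00 | 8.0 | 6.3 | 26.7% (true) |
| 5% | 1.05 | 8.4 | 6.6 | 28.5% |
| 10% | 1.11 | 8.9 | 7.0 | 30.5% |
| 15% | 1.18 | 9.4 | 7.4 | 32.6% |
| 20% | 1.25 | 10.0 | 7.9 | 34.8% |
| 30% | 1.43 | 11.4 | 9.0 | 39.7% |

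Example: at s = 10%, 8/0.90 = 8.9 and 6.3/0.90 = 7.0.

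**4. Check at the planned size**

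A simulation used 28 patients, a true median of 6.3 months, administrative censoring uniform between 12 and 32 months, and 3,000 trials for each s. The typical estimated median was about 6.0 months with deaths counted against 6.9 with deaths censored at s = 10%, and about 6.0 against 7.9 at s = 20%. In no simulated trial was the progression-only median below the progression-or-death median.

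**The case against.** The best case for leaving this alone has four parts.

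- **PFS decides nothing.** It is secondary and descriptive, without hypothesis or threshold; the trial's conclusion rests on responder counts. This is true and limits the reach of the error, but it does not make the definition correct.
- **Censoring is inferred.** The protocol does not say how a death without progression is coded, and a separate analysis plan might. Censoring is nonetheless what the stated event implies under Kaplan-Meier. The protocol has fixed the event three times, once within its own statistical analysis section. An analysis plan that follows it inherits the error, and one that does not contradicts it.
- **The size has no anchor in the protocol.** This stands: s is unknown, and at s = 0 there is no bias. Life expectancy above 12 weeks and scans every 6 weeks argue against a large s, although ECOG 2 is admitted. With 28 events, an approximate 95% interval for an exponential median spans factors exp(±1.96/√28), or 0.69 to 1.45, so a shift of 5 to 11% is well inside sampling error. But the interval reflects chance, while this shift always goes the same way.
- **The introduction compares published late-line studies with one another.** It does not promise a comparison with this trial. That is correct, and the finding does not need such a promise: a median labelled PFS will be read as PFS.

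**Conclusion.** The concern holds. As written, the endpoint is time to progression under the name PFS, and it is out of line with the protocol's own definition of duration of remission. With deaths without progression censored at the date of death, the reported curve can equal true PFS or exceed it, but not fall below it. Under constant hazards the median is overstated by about 5% at s = 5%, 11% at 10% and 25% at 20%, and not at all if nobody dies without documented progression. The omission of death is certain from the text; the size rests wholly on the assumed s. The primary response-rate decision is not touched. The remission-time wording in Section 7.3 is a smaller, related inconsistency.

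**What to change.** In Sections 2, 3.7.1 and 5.1.3.2, replace the PFS sentence with: *PFS is the time from therapy initiation to first RECIST 1.1 progression or death from any cause, whichever occurs first; patients alive without progression are censored at their last evaluable tumour assessment.* This censoring date matches the one Section 3.7.1 already uses for duration of remission.

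In Section 7.3, end remission time at progression or death, as Sections 3.7.1 and 5.1.3.2 do.

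Renaming the endpoint time to progression would also make the label honest, but the trial would then have no PFS result.

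The cost is wording only. Sections 3.7.4.1 and 3.8.5 already provide for survival status and date of death, so no new data are needed. The reported median may be somewhat shorter.

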**5.1.3.3** **Exploration biomarker analysis**

PD-L1 expression, TMB, molecular alteration profile, tumor immune-microenvironment, plasma exosome miRNA.

**5.1.3.4 Safety analysis**

The adverse events will be summarized according to the NCI-CTCAE 5.0. The adverse events will be summarized according to the severity of the adverse event associated with study drug. The descriptive summary of laboratory values is mainly for abnormal values. Laboratory abnormalities will also be summarized according to the most severe grade in NCI-CTCAE 5.0.

6 **Adverse Events**

**6.1** **Detection of adverse events**

The adverse events of the subjects must be closely monitored including clinical symptoms and laboratory tests. The severity grade and relationship with the drugs should be evaluated. The investigator was responsible for evaluating the relationship between all adverse events and the drugs. However, the primary investigator can entrust other researchers participating in this study to judge, but still need to be responsible for this. The researcher must provide a list of qualified and entrusted personnel.。

**6.2 Definition of adverse events**

**6.2.1 adverse events**

An adverse event is any adverse medical event that occurs to a patient or a subject when treated with the study drug. There may be no causal relationship between adverse events and treatment. Therefore, an adverse event can be any adverse and meaningless sign (including abnormal laboratory test), symptom or disease temporarily associated with the study drug used, regardless of whether the event is drug-related or not.

Adverse events (whether drug-related or not) in human body may include the following aspects:

• Adverse events occurred during the use of drugs by professionals;

• Adverse events caused by overdose (whether intentional or unintentional);

• Adverse events caused by drug abuse;

• Adverse events caused by discontinuation of medication;

• Adverse events that may be purely due to the patient's participation in the study (e.g. adverse events due to withdrawal of antihypertensive drugs during washout period or serious adverse events), which must be reported as adverse events even if they are not related to the study medication.

The adverse events were described according to CTCAE 5.0.

**6.2.2 Serious adverse events**

Serious adverse events refer to all adverse events that meet one of the following conditions：

• Causing death;

• Life threatening;

• Causes the patients to be hospitalized or the hospitalized patient prolongs the hospitalization time;

• Cause permanent or obvious loss of working ability or disability;

• Congenital malformation or defect;

• Serious medical events

Life threatening**:** The term "life-threatening" is defined as "serious" and refers to the risk of death of the subject when an adverse event occurs. It does not refer to those adverse events that may lead to death if the situation is assumed to worsen.

Hospitalization: all adverse events causing hospitalization or prolonging the hospitalization time were defined as “serious adverse event”, expect for the following aspects:

- - - Stay in hospital for no more than 12 hours
      or
    - Hospitalization was planned before the start of this study (i.e. scheduled surgery or elective surgery before the start of this study);

or

- - - Hospitalization was not associated with adverse events (e.g., hospitalization for convalescent purposes).

**Disability：**someone's ability to engage in daily life is seriously impaired.

**Serious medical events**：Any adverse event may harm the subject and may require intervention to prevent a more serious situation, which can be considered as serious medical event. Serious medical events should be determined according to the WHO terminology of adverse events. The reason why these events are reported as serious adverse events is that they may be related to the serious disease stats, and as SAE reports, it can ensure special attention and promote necessary actions compared with other reporting methods.

**6.2.3 Unexpected adverse events**

Unexpected adverse events refer to any adverse events which are inconsistent with the researcher's Manual (or the instructions in the package of the marketed products). It is also an integral part of the report of unexpected adverse events to supplement the important information about the characteristics or severity of known and recorded adverse events. For example, events that are more special or serious than those described in the researcher's manual should be considered "unexpected". For example: (a) interstitial nephritis followed by acute renal failure of records adverse events; And (b) hepatitis first reported as acute hepatic necrosis.

**6.2.4 Relationship between adverse events and research drugs**

The evaluation of the relationship between an adverse event and the study drug is a comprehensive clinical judgment based on all the information obtained when completing the case report form.

Evaluation of "irrelevant" situations may include:

- - 1. There are clear other explanations, such as traumatic bleeding at the surgical site;
       or
    2. Unreasonable, for example, the subject was hit by a car, but there was no evidence that the drug-induced disorientation caused the event; Or cancer developed just a few days after the start of administration.

A "yes" assessment indicates there is a reasonable reason that the adverse event may be related to the study medication.。

When the investigators evaluated the relationship between adverse events and study drugs, the following factors should be considered：

– The adverse event should occur after administration. The interval between medication and the occurrence of the adverse event should be considered in clinical evaluation.

– The event disappeared after stopping administration (stopping stimulation) and recurred after re-administration (repeated stimulation): when analyzing the clinical process of the suspicious event, the response of the subject after stopping administration (stopping stimulation) or after re-Administration (repeated stimulation) should be fully considered.

– Basic diseases, concomitant diseases and intermittent diseases: the natural course of disease, treatment process and all other diseases that patients may have in each report should be evaluated;

– Combined medication or treatment: other drugs taken by the subject or other treatments received by the subject should be checked to determine whether one of them may cause the adverse event;

– Known response patterns of a class of drugs: clinical/preclinical

–Pharmacology and pharmacokinetics of the test drug: the pharmacokinetic characteristics (absorption, distribution, metabolism, and excretion) of the test drug should be considered in combination with the individual pharmacodynamic response of each subject.

**6.2.5 Record of adverse events**

All adverse events occurred after the informed consent should be signed by the subjects and must be completely recorded in the case report form each subject.

The records must be supported by original data. Laboratory abnormalities associated with clinically treatment (such as those that lead to early withdrawal from the study, need treatment or cause obvious clinical manifestations, or those are considered to be associated with treatment by investigators) should be reported as adverse events. Each event should be described in detail, including the start and end time, severity, relationship with the treatment, measures and the outcome of the event.

